### Outcome variables

The primary outcome variable will be the score on the Action Research Arm test (ARAT). Secondary outcome variables are the scores on the Motricity Index (MI) of the arm, Fugl-Meyer for the arm (FM-arm), Nine Hole Peg test (NHPT), Erasmus modification of the Nottingham Sensory Assessment (EmNSA), Motor Activity Log (MAL), and Stroke Impact Scale (SIS version 3.0). All assessments will be applied to all patients at t0, t1, and t2.

Non-parametric statistics for independent samples will be used [81]. A Kruskal-Wallis test will be used to examine whether improvements before and after intervention (from t0 to t1) were significantly different between the three intervention groups (i.e., BATRAC, CIMT, and DMCT). When a significant difference is found between the three groups, a *post-hoc *Mann-Whitney U test will be applied to reveal which groups (CIMT, BATRAC, or DMCT) differ significantly from each other. The same procedure will be used for observed changes after the 6 weeks retention period, i.e., from t1 to t2.

The ARAT is a valid, reliable, and responsive performance test [82] of the ability to perform gross movements and to grasp, move, and release objects differing in size, weight, and shape [83]. The minimal clinically important difference is set at about 10% of the scale's range, i.e., 6 points [84]; improvement by > 10 points is defined as return of dexterity [17].

The MI will be used to measure strength in upper extremities [85]. Higher scores represent greater strength in the upper limb. This instrument provides a reliable and valid assessment of the presence of paresis in stroke patients by testing 6 functions rated for each limb [64,85].

The FM arm score is a reliable and valid motor performance test consisting of 33 tasks performed by the affected upper limb [86,87]. The FM-arm test evaluates the ability to make movements outside the synergistic pattern. Performance on each task is rated as 0, 1, or 2, with higher rates representing better performance. The FM-arm measure will be used as the sum of 33 ratings (possible range 0 to 66 points).

The NHPT is a reliable and valid test that measures manual dexterity [88,89]. It measures the speed with which a patient grasps and inserts (and removes) 9 pegs into a grid of vertical holes. The test will be discontinued after 50 s if the patient is still unable to insert any pegs. The NHPT measure for each hand is calculated by the number of pegs placed per second. The affected as well as the unaffected hand will be measured. Reliability and validity have been assessed and norms are available [88,89].

The EmNSA is a 3 point ordinal scale that measures sharp-blunt discrimination, two-point discrimination, and limb proprioception. The EmNSA will be restricted to the paretic upper limb (i.e., fingers, hand, and forearm). With the exception of the two-point discrimination item, intra- and interrater reliability of tactile sensations, sharp-blunt discrimination and proprioception items are good to excellent (Kappa: 0.58 to 1.00, [90]).

A translated and adapted version of the MAL will be used [91], which contains the 14 original activities, 11 additional activities, and 1 optional activity chosen by the patient. Reliability and validity of the MAL has been demonstrated in a number of studies [91]. The MAL will be administered to each applicant and, if available, their caregivers. It will be used to independently rate how well (5-point Quality of Movement [QOM] scale) and how much (5-point Amount of Use [AOU] scale) the paretic arm was used spontaneously to accomplish 26 activities of daily living outside the laboratory [84,92].

The arm-hand domain of the SIS (version 3.0) will be used to evaluate patients' perceived outcome for the paretic upper limb. Version 3.0 of the SIS is a full-spectrum health status interview that measures changes in 8 impairments, function and quality-of-life subdomains following stroke and will be used as a secondary outcome measure [93]. Each domain will be analyzed separately. The upper limb part of the SIS includes 5 questions about patients' perceived competency to keep their balance, to transfer, to walk in the house and negotiate stairs, to get in and out of a car, and to move about in their own community. Each item is scored from "not difficult at all" to "cannot do at all" on a 5 point rating scale. A difference of 5 points (10%) on the "hand function" domain of the SIS is perceived as clinically relevant [28]. The SIS has shown excellent clinimetric properties in terms of concurrent and construct validity, test-retest reliability, and responsiveness [94].

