In light of contrasting results and divergent perspectives regarding underlying mechanisms of current interventions [31], their potential dependence on the neurological characteristics of stroke survivors will also be a topic of investigation in the ULTRA-stroke program. It has been proposed that the effectiveness of CIMT is dependent on CST integrity [32-34], which is essential for motor control of the distal part of the upper limb. On the other hand, BATRAC may be expected to be less dependent on the integrity of the CST, as it appears to induce reorganizations in cortical inter- and intrahemispheric networks [21,22]. To cope with this issue, participants will be categorized in terms of their motor ability of the distal part of the arm [8].

In short, we hypothesize that both modified CIMT and modified BATRAC significantly improve upper limb function when compared to DMCT. Modified CIMT is expected to have a larger impact on those subjects who already showed some dexterity at recruitment than on subjects that were more restricted in this regard, given the proposed importance of CST integrity for motor control of the distal part of the upper limb [25]. Modified BATRAC, on the other hand, is expected to be also effective for the latter group of subjects, thanks to influences stemming from and reorganizations in the contralesional hemisphere (see also [35-37]). The effects of modified BATRAC and modified CIMT are both expected to sustain during the follow-up period of 6 weeks. To uncover the mechanisms associated with intervention-induced functional improvement, three kinds of analysis will be included.

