### Recruitment

Sixty patients, admitted to the Rehabilitation Centre Amsterdam (RCA), who meet the criteria within 6 months after stroke onset will be recruited. Both in- and outpatients will be enrolled.

The inclusion criteria are: a first-ever ischemic or hemorrhagic stroke in one of the hemispheres, as verified by CT and/or MRI scan; an upper limb deficit, however with minimal control of the paretic wrist and fingers (i.e., able to execute at least 10° of active wrist extension, at least 10° of thumb abduction/extension, and at least 10° extension in at least 2 additional digits); a score on the Action Research Arm Test (ARAT) of less than 53 points; between 18 and 80 years of age; written or oral informed consent; sufficient motivation to participate.

The exclusion criteria are: upper extremity orthopaedic limitations; not being able to communicate (i.e., < 4 points on the Utrecht Communication Observation, UCO [63]); a Mini Mental State Examination (MMSE) score of < 24 points [64]. Patients with a pacemaker or metallic implant will be recruited. However, they will not be subjected to MEG-recordings given the interference with the magnetic signal. There will be no restrictions with respect to gender, ethnicity, or socio-economic status.

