### Design

The intake procedure will take place the week following informed consent. After the intake procedure, which will include the first assessment of outcome variables, patients will be stratified in those with some dexterity and those with minimal control of paretic wrist and finger extension. Patients with some dexterity are able to execute > 10° finger extension of each metacarpophalangeal and interphalangeal joint of all digits and > 20° wrist extension. Patients with minimal control are those who meet the criteria of inclusion (i.e., able to execute at least 10° of active wrist extension, at least 10° of thumb abduction/extension, and at least 10° extension in at least 2 additional digits), but not (yet) the criteria of some dexterity. After stratification, patients will be randomized in permuted blocks and allocated to one of the three intervention groups (i.e., modified BATRAC, modified CIMT, or DMCT). Concealed allocation is effectuated with an online, computerized randomization procedure according to the minimization method [65]. Other therapists and social workers will provide regular care depending on patient needs.

After the first assessment and randomization, an intervention period will take place for 6 consecutive weeks. The effects of the interventions are examined using a pretest-posttest design. The pretests (t0) are performed in the week prior to intervention and posttests (t1) are performed in the week after intervention. The degrees to which changes are sustained are examined using retention tests (t2), 6 weeks after completion of the intervention. Figure 1 shows the time schedule for effectuating the entire protocol. (Figure 1.)

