### Peripheral stiffness

Endpoint mechanical behavior of the paretic wrist, resulting from a mix of visco-elastic (intrinsic) and proprioceptive reflex (reflexive) properties, will be assessed under both passive and active conditions using a haptic robot ('Wristalyzer', Moog FCS Inc., Nieuw-Vennep, The Netherlands). This powerful, force-controlled manipulator applies force- and position perturbations to the paretic wrist, while the interaction with the patient, in terms of forces and joint angles, is measured. A haptic controller, which overrules the dynamics of the manipulator with imposed virtual dynamics, is used to apply perturbations. The result is that, to the patient, the manipulator behaves like a mass-spring-damper system. After assessment of the range of motion (ROM) and maximal force, both towards flexion and extension, a number of perturbation tests under both passive and active conditions will be applied. Using system identification in the frequency domain [39,95,96], the intrinsic vs. reflexive stiffness is calculated from the time series of net moment and wrist position. Surface EMG (16-channel Biotel 99 EMG amplifier, Glonner Electronic GmbH, Munich, Germany) is measured for additional validation. From the time records of position and force, frequency response functions (FRFs) will be estimated. FRFs are transfer functions that express the structural response to an applied force in the frequency domain. Given a model structure and an appropriate estimate of the intrinsic component, an estimate of the reflex gains for length and velocity can be obtained from the FRFs [39,95,96]. For both intrinsic and reflexive properties, a repeated measures AN(C)OVA will be performed to detect differences over time and between groups (intervention/stratification).

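### The primary ARAT test leaves out the dexterity stratum used in randomisation and adjusts for baseline only by subtraction: valid, but it loses power if stratum or baseline predicts recovery

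*Protocol article*

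**What the plan says.** Under Outcome variables the article names the endpoint, "The primary outcome variable will be the score on the Action Research Arm test (ARAT", and the class of analysis, "Non-parametric statistics for independent samples will be used [81". The primary test follows: "A Kruskal-Wallis test will be used to examine whether improvements before and after intervention (from t0 to t1) were significantly different". If it is significant, a "Mann-Whitney U test will be applied to reveal which groups (CIMT, BATRAC, or DMCT) differ significantly from each other". No stratum or covariate term appears.

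Under Design, before allocation, "patients will be stratified in those with some dexterity and those with minimal control of paretic wrist and finger extension". ARAT is measured in everyone at t0, t1 and t2. Under Recruitment, patients "who meet the criteria within 6 months after stroke onset will be recruited". The Background section expects the treatment effect to depend on the stratum: "Modified CIMT is expected to have a larger impact on those subjects who already showed some dexterity at recruitment" than on the more restricted patients. The stratum does enter one stated analysis, the repeated measures AN(C)OVA of the stiffness outcomes, "to detect differences over time and between groups (intervention/stratification".

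**The concern.** Stratified allocation makes the arms alike on the stratum. An analysis that then ignores the stratum keeps the between-stratum variation in its error term. If the strata recover differently, the test takes the arm contrast to be noisier than it is, so it rejects too rarely both under the null and under a true effect. Subtracting t0 ARAT fixes the slope on baseline at 1, and any remaining relation between change and baseline also stays in the error.

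The stake is efficiency. The trial is sized at 15 evaluable patients per arm, and the primary outcome is analysed with less information than the stiffness outcomes, although stratum and t0 ARAT are both in hand at no extra cost.

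**Working it through.** **1. The plan's own figure.** From Power analysis: alpha 0.017, power 80%, variance 26 (SD 5.10), difference 6, ratio 1.
- (z₀.₉₉₁₅ + z₀.₈₀)² = (2.387 + 0.842)² = 10.42; the plan prints 10.43.
- n = 2 × 10.43 × 26/36 = 15.07 per group; the plan prints 15.
- 15/(1 − 0.25) = 20 per group, or 60 in all.
- The formula gives 79.8% power at 15 per group.

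The figure reproduces. It is a normal-theory comparison of two means, not a rank-test calculation.

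**2. What stratum adjustment removes.** Assume equal strata and total change variance 26. If spontaneous gains are a and b, the between-stratum part is ((a − b)/2)². Power ≈ Φ(6/√(2σ²/15) − 2.387), with σ² the within-stratum variance.

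| Gains | Between | Within | Formula power, adjusted |
|---|---|---|---|
| 6/6 | 0 | 26 | 79.8% |
| 9/6 | 2.25 | 23.75 | Φ(3.372 − 2.387) = 83.8% |
| 12/6 | 9 | 17 | Φ(3.985 − 2.387) = 94.5% |

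**3. Simulation of the stated procedure.** Kruskal-Wallis at 0.05, then Mann-Whitney at 0.017, against ANCOVA at 0.017 with t0 ARAT and stratum; 15 per arm; one arm 6 points better. Assumed, not in the documents: baseline means 15 and 40 with SD 8, the lower stratum gaining more, ARAT maximum 57. In each range the first figure has the ceiling and the second has none.

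| Gains | Stated procedure | ANCOVA |
|---|---|---|
| 6/6 | 63-70% | 71-75% |
| 9/6 | 53-68% | 73-80% |
| 12/6 | 42-62% | 87-93% |

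At 12/6 the pairwise null size of the stated procedure is about 0.3% against a nominal 1.7%.

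**4. How firm these figures are.** Fifteen does not halve. I reran the simulation (3,000 runs per setting). The stated-procedure figures for 9/6 and 12/6 reappear when the control arm has 8 patients in the faster-recovering stratum and the treated arm 7, which shifts the unadjusted contrast by 3/15 = 0.2 and 6/15 = 0.4 points. With the split matched at 8 and 8, the stated procedure has about 58-72% at 9/6 and 54-71% at 12/6. ANCOVA hardly moves (74-81% and 87-93%). The loss at 12/6 is then about 21 to 33 percentage points.

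**5. A second model.** Total variance is held at 26, data are normal without a ceiling, and r is the assumed correlation of change with stratum and baseline together.

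| r | Stated, 15 per arm | ANCOVA, 15 per arm | Kruskal-Wallis null size (nominal 5%) |
|---|---|---|---|
| 0 | 72% | 77% | 4.2% |
| 0.3 | 73% | 81% | 4.8% |
| 0.5 | 73% | 88% | 2.7% |
| 0.7 | 72% | 97% | 2.0% |

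At 20 per arm (no drop-out) and r from 0 to 0.5, it is 85-88% against 88-97%.

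**6. Baseline alone.** With equal variances at t0 and t1 and correlation ρ, the ANCOVA-to-change variance ratio is (1 + ρ)/2. The assumed baselines have variance 64 + 12.5² ≈ 220. With change variance 26, ρ = 1 − 26/(2 × 220) ≈ 0.94 and the ratio is about 0.97. In these settings the gain comes mainly from the stratum.

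**The case against.** The strongest case against is that the plan is valid as it stands. A conservative test protects the type I error, and rank tests are a defensible choice for a bounded scale with entry below 53 points. Skewed data could favour ranks over a linear model. All of this stands, and it limits the point to efficiency.

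Four stronger readings are tempting, and the documents do not support them.
- **Baseline is ignored.** It is not: the analysed variable is the change from t0, so baseline is subtracted. Only adjustment by regression is absent.
- **The strata exist because spontaneous recovery differs between them.** The Background section argues from effect modification: CIMT is expected to depend on corticospinal integrity, BATRAC less so. No section gives spontaneous gain by stratum.
- **The plan can give no difference in ARAT points.** The article names tests and does not exclude estimates. A Hodges-Lehmann shift with an interval would fit those tests, and an article may leave such reporting to the full plan.
- **Power falls to 37% at gains of 12/6.** That figure takes 26 as the within-stratum variance and adds the stratum spread on top, which makes a noisier trial than the one sized. The article describes 26 as the expected variance of the sample.

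**Conclusion.** The point holds as an efficiency recommendation on a stated method. The primary test does not use the randomisation stratum and handles t0 ARAT only by subtraction. In every setting examined ANCOVA had the higher power. With no stratum difference the gain is small, about 5 to 8 percentage points. It grows to tens of points only if strata differ by several ARAT points in spontaneous recovery, and nothing in the documents says whether they do. The power figures are therefore illustrations under stated assumptions (15 evaluable per arm, total change variance near 26, equal strata, a 5% gate and 0.017 per pair), not estimates for this trial. The sample size is not arithmetically wrong, and false positives are not inflated.

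**What to change.** Make the primary analysis a model of t1 ARAT on arm, t0 ARAT and dexterity stratum. Report the three pairwise adjusted differences in ARAT points with confidence intervals at the corrected alpha, so that they can be read against the 6 points used for sizing.

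If a non-parametric primary test is preferred, use a stratified rank test (van Elteren) or a covariate-adjusted rank test, which keeps most of the gain when strata differ. In a simulation with within-stratum variance 26 and gains of 9/6, a covariate-adjusted rank test had 64% power, against 54% unadjusted and 70% for ANCOVA.

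Keep Kruskal-Wallis and Mann-Whitney as a sensitivity analysis. Add an arm-by-stratum term as a secondary analysis for the hypothesis in the Background section; the main-effects model does not test it. Weeks since stroke is an optional further covariate, given the six-month entry window, but its benefit was not quantified.

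The cost is analysis wording only, since stratum and t0 ARAT are already collected. The small downside is a linear-model assumption on a bounded scale, which the rank-based sensitivity analysis covers.

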### Power analysis

The number of patients is based on a statistical power of 80% (preventing Type II error) with an alpha of 5% (preventing Type I error) for detecting a meaningful difference of 6 points on the ARAT as the primary measurement of outcome and expecting 15% drop-out. The statistical power for detecting 10% or 6 points difference between groups is based on the following power calculation:

(Z_1-α/2 _+ Z_1-β_)^2 ^= 10.43 (assuming an alpha of 0.017, corrected for multiple testing with 3 groups and a Beta of 0.80)

σ2 (expected variance of sample on ARAT) = 26

Δ2 (assumed difference in favour ARAT) = 36

r (expected ratio between intervention groups) = 1

Expected numbers needed per intervention group (N_per group_) = 15 (excluding expected drop out of less than 25%).

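### Retention is tested only as a between-arm difference in t1-to-t2 change, so a non-significant result is the hoped-for answer and the difference from DMCT at t2 is never estimated

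*Protocol article*

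**What the plan says.** The Background section sets out two linked hypotheses. The first is efficacy against dose-matched conventional treatment (DMCT): "both modified CIMT and modified BATRAC significantly improve upper limb function when compared to DMCT". The second is durability: "The effects of modified BATRAC and modified CIMT are both expected to sustain during the follow-up period of 6 weeks". The Design section gives the t2 visit its purpose: "The degrees to which changes are sustained are examined using retention tests (t2), 6 weeks after completion of the intervention".

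The Outcome variables section fixes the analysis of the ARAT and the other clinical scales. A Kruskal-Wallis test examines whether "improvements before and after intervention (from t0 to t1) were significantly different between the three intervention groups". Pairwise testing is conditional on that result: "When a significant difference is found between the three groups, a *post-hoc *Mann-Whitney U test will be applied". Retention is then covered in one sentence: "The same procedure will be used for observed changes after the 6 weeks retention period, i.e., from t1 to t2".

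The section states no between-arm contrast at t2, no t0-to-t2 contrast, and no margin or interval that would define a sustained effect. The repeated measures AN(C)OVAs under Peripheral stiffness and Interlimb interactions concern the mechanism measures, not the ARAT.

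**The concern.** The durability hypothesis says that a benefit seen at t1 is still there at t2. If so, the arms do not differ in their change from t1 to t2. The planned test takes that very state as its null hypothesis, so the hypothesis is supported, at best, by failure to reject. In a trial sized at about 15 evaluable patients per arm, failure to reject is weak evidence of anything.

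A significant result has its own difficulty. It may reflect loss in an active arm, late catch-up in DMCT, or late gain in an active arm, and it does not say who is better at t2. An arm that gained 8 points and lost 2 ranks below an arm that gained 0 and lost 0 on this contrast, although it is 6 points ahead at t2. The comparison also starts from t1, a value that treatment has already affected.

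At stake is whether the trial can report, with an estimate and its uncertainty, how the arms stand 6 weeks after treatment ends.

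**Working it through.** **Inputs from the documents**
- Difference of interest: 6 ARAT points (Power analysis; Outcome variables gives the same figure as the minimal clinically important difference).
- Variance 26, so SD = √26 = 5.10 (Power analysis, described as the expected variance of the sample on the ARAT).
- Constant 10.43, "assuming an alpha of 0.017, corrected for multiple testing with 3 groups" (Power analysis).
- 60 patients, 20 per arm. Power analysis gives drop-out as 15% in one place and as less than 25% in another: 20 × 0.85 = 17 and 20 × 0.75 = 15 evaluable per arm.

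**The plan's own figure.** n per arm = 2 × 10.43 × 26 / 36 = 15.07, against 15 stated. It reproduces.

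**What the retention contrast measures.** Let D01, D12 and D02 be the active-minus-DMCT differences in mean change over t0–t1, t1–t2 and t0–t2. Then D02 = D01 + D12. The durability hypothesis concerns D02 when D01 is positive. The planned test concerns only D12.

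**Simulation of the planned test.** Kruskal-Wallis at 5%, normal changes, 15 per arm, both active arms sharing the same benefit over DMCT. The SD is 5.1 for every change score. Using 5.1 for t1–t2 and t0–t2 change is an assumption.

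| Benefit at t1 → t2 | D12 | t1–t2 test rejects | t0–t2 test rejects |
|---|---|---|---|
| 6 → 6 (fully kept) | 0 | about 5% | 87–89% |
| 0 → 0 (never present) | 0 | about 5% | 4–5% |
| 6 → 3 (half lost) | −3 | about 32% | 32–35% |
| 6 → 0 (all lost) | −6 | about 88% | 4–5% |
| 0 → 6 (late gain) | +6 | about 88% | 88–89% |

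The first two rows are the main point. On t1–t2 change a fully kept benefit and no benefit give the same result; on t0–t2 change they separate. The last two rows show that rejection on t1–t2 is equally likely in opposite situations at t2.

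**Sensitivity to the unknown SD of t1–t2 change** (half of a 6-point benefit lost):

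| SD | 15 per arm | 17 per arm |
|---|---|---|
| 3 | about 75% | about 82% |
| 4 | about 50% | about 55% |
| 5.1 | about 32% | about 36% |
| 7 | about 18% | about 21% |

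The figures barely change if one arm rather than two loses the 3 points.

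**Precision.** The 95% half-width for a pairwise difference in t1–t2 change is t(0.975; 2n−2) × SD × √(2/n). At n = 15 and SD 5.10 this is 2.048 × 5.10 × 0.365 = 3.8 points; at n = 17 it is 3.6. Over SD 3 to 7 it runs from 2.1 (n = 17) to 5.2 (n = 15). At the trial's own SD the half-width exceeds half of the 6-point threshold.

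**The case against.** The strongest reply is that the t1–t2 test should not be read alone. Whether a benefit exists is the job of the t0–t1 test, which does distinguish a kept benefit from none. Change after treatment is a direct measure of how far gains last, which is how the Design section words the aim, and complete loss of a 6-point benefit would be detected about 88% of the time at SD 5.1. All of this stands. What remains is that combining the two tests is informal: no estimate, interval or test of the t2 difference from DMCT is stated, and partial loss is readily missed.

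Several stronger readings are tempting and not supported:
- A reader might infer that the plan cannot show a benefit at all. It can, through the t0–t1 comparison.
- A reader might infer that the investigators will take non-significance as proof of retention. The article states no such decision rule.
- A reader might infer that two windows inflate the type I error of the efficacy claim. The Design section gives the windows different roles, and the Outcome variables section does not set 5% for each.
- A reader might infer that a t0–t2 contrast is more powerful. For the same difference and SD it is not: a remaining 3-point difference is missed about as often as a 3-point loss. The gain is that it addresses the right quantity.

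An unseen analysis plan may add a t0–t2 contrast. The point rests on the retention contrast the article does fix, which suits the stated hypothesis poorly as the only one.

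**Conclusion.** The concern holds as a mismatch between the durability hypothesis and the contrast chosen to examine it. Under that hypothesis the null of the planned test is true, and non-significance neither separates a kept benefit from none nor rules out losing half of it: detection is about 18% to 75% with 15 per arm over SD 7 to 3. A significant result would not establish which arm is better at t2.

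The detection figures assume normally distributed changes, a 5% Kruskal-Wallis test and an SD of t1–t2 change that the article does not give; hence the range. The structural point, that a fully kept benefit and no benefit give the same t1–t2 contrast, needs none of these assumptions. The main t0–t1 comparison is untouched, so this is a recommended change and not one the trial depends on.

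**What to change.** In Outcome variables, replace the retention sentence with three statements:
1. The t0-to-t1 comparison of the ARAT remains the main efficacy comparison.
2. Retention is assessed by comparing the arms on ARAT change from t0 to t2, or on the t2 score adjusted for t0 and the dexterity stratum, with pairwise differences and confidence intervals read against the 6-point threshold.
3. Change from t1 to t2 is reported as a supporting estimate with a confidence interval. If it is to carry a claim that effects are sustained, a margin is stated in advance.

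The cost is one paragraph of text. No extra visit or measurement is needed, since "All assessments will be applied to all patients at t0, t1, and t2".

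### Retention of the clinical benefit is tested only as an arm difference in t1–t2 change, so the trial's own hypothesis is that test's null, and no stated test asks whether an arm difference remains at t2

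*Protocol article*

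**What the plan says.** The Background frames the hypothesis as improvement with modified CIMT and modified BATRAC relative to DMCT, and adds: "The effects of modified BATRAC and modified CIMT are both expected to sustain during the follow-up period of 6 weeks". The Design section gives the purpose of the last visit: "The degrees to which changes are sustained are examined using retention tests (t2), 6 weeks after completion of the intervention".

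Outcome variables then fixes the tests for the ARAT and the secondary clinical outcomes. For the treatment window, "A Kruskal-Wallis test will be used to examine whether improvements before and after intervention (from t0 to t1) were significantly different" between the three arms, with Mann-Whitney U tests between pairs if the overall test is significant. For follow-up, "The same procedure will be used for observed changes after the 6 weeks retention period, i.e., from t1 to t2". The same section says "All assessments will be applied to all patients at t0, t1, and t2", so t0–t2 change will be available for every patient who completes.

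For these outcomes the article states no t0–t2 comparison, no comparison of arms at t2, and no equivalence or non-inferiority margin. The stiffness and interlimb measures are planned with repeated measures AN(C)OVA and lie outside this point.

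**The concern.** The follow-up test does not match the follow-up hypothesis. If the benefit over DMCT persists, the arms move in parallel after t1 and the test has nothing to find. Failing to reject a difference with about 15 to 17 patients per arm and no margin is not evidence that a benefit was kept.

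If the test does reject, two clinically opposite histories fit: trained patients lost ground, or DMCT patients caught up. Catch-up is plausible because patients are enrolled within 6 months of stroke and may still be recovering.

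At stake is the conclusion at t2. The trial could finish without a stated test of whether any arm is better off six weeks after treatment ends. This is not a detail left to an unseen analysis plan, because the article itself names the t1–t2 interval.

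**Working it through.** **1. The design figure.** Inputs from Power analysis: variance 26 (SD √26 = 5.10), difference 6 points (36 squared), multiplier 10.43. n = 2 × 26 × 10.43 / 36 = 15.07 per arm, and the article states 15, so the figure reproduces. Sixty patients give 20 per arm, which is 17 after 15% drop-out and 15 after 25%. The calculation is sized on a 6-point difference and does not address retention.

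**2. What the t1–t2 contrast can see.** Write D for trained arm minus DMCT. Then D(t0–t2) = D(t0–t1) + D(t1–t2). Take D(t0–t1) = 6.

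| What happens after t1 | Trained, t1–t2 | DMCT, t1–t2 | D(t1–t2) | D(t0–t2) |
|---|---|---|---|---|
| Benefit fully kept | 0 | 0 | 0 | 6 |
| All arms lose 6 | −6 | −6 | 0 | 6 |
| Trained arms lose half | −3 | 0 | −3 | 3 |
| DMCT catches up by half | 0 | +3 | −3 | 3 |
| Trained arms lose all | −6 | 0 | −6 | 0 |
| DMCT catches up fully | 0 | +6 | −6 | 0 |

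The hypothesised case is D(t1–t2) = 0, the null. Loss and catch-up of equal size give the same contrast. Rows 1 and 2 show that D(t0–t2) in turn cannot tell whether patients kept their own gains. This step needs no assumed figure.

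**3. Size.** The document gives neither the SD of t1–t2 change nor its correlation with t0–t1 change, so both are assumed and varied. There are three arms, both trained arms gain 6 points more than DMCT by t1, t0–t1 variance is 26, changes are rounded to whole points, and the tie-corrected Kruskal-Wallis test is run at 5% in 20,000 simulated trials per cell.

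- Measurement-error model: error makes up a share s of the 26, and true change after t1 has variance k times the true t0–t1 variance. Then SD(t1–t2) = √(26 × [s + k(1 − s)]).
- Independent-change model: t1–t2 change is independent of t0–t1 change, with SD 5.10 or 3.57 (0.7 × 5.10).

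Percentages are for 15 / 17 per arm.

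| Assumption | SD t1–t2 | Half lost: t1–t2 test non-significant | Fully kept: t0–t2 test significant | 3 points left: t0–t2 test significant | DMCT catches up fully: t1–t2 test significant |
|---|---|---|---|---|---|
| s = 30%, k = 0 | 2.79 | 18 / 14 | 88 / 93 | 32 / 35 | >99 / >99 |
| s = 50%, k = 0 | 3.61 | 41 / 35 | 89 / 93 | 32 / 36 | >99 / >99 |
| s = 80%, k = 0 | 4.56 | 60 / 56 | 88 / 93 | 32 / 36 | 95 / 97 |
| s = 30%, k = 0.25 | 3.51 | 39 / 33 | 83 / 87 | 28 / 32 | >99 / >99 |
| s = 50%, k = 0.25 | 4.03 | 51 / 45 | 84 / 89 | 29 / 33 | 98 / 99 |
| s = 80%, k = 0.25 | 4.70 | 63 / 59 | 87 / 91 | 31 / 35 | 93 / 96 |
| Independent | 5.10 | 68 / 64 | 58 / 65 | 17 / 20 | 89 / 93 |
| Independent | 3.57 | 41 / 34 | 72 / 78 | 22 / 25 | >99 / >99 |

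When the benefit is fully kept, or when all arms lose 6 points, the t1–t2 test is significant in about 5% of trials. It cannot tell these two cases apart.

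**4. Pairwise follow-up test.** Normal approximation, 17 per arm, alpha 0.017, SD 5.10, 3-point loss: 3 / (5.10 × √(2/17)) = 1.72. The critical value is 2.39, and Φ(1.72 − 2.39) is about 0.25. Power is about 25%.

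**The case against.** The strongest reply is that the Design section speaks of changes being sustained, which can mean patients keeping their own gains. On that reading t1–t2 change is the natural quantity and t0–t2 is not: if all arms lose 6 points, t0–t2 stays significant in about 65% of trials at 17 per arm with independent changes of SD 5.10, although no arm kept its gain. This stands, and it is why t0–t2 alone is not enough. It does not rescue the stated test, because a between-arm test of t1–t2 change is equally silent when every arm loses the same amount.

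It may also be said that the t0–t2 difference is the sum of the two window differences. That holds for means, but the plan states rank tests, and two rank tests do not add up to a test of the sum.

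Three stronger readings are tempting and are not supported:

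- A reader might infer that a non-significant t1–t2 result will be reported as a sustained effect. No such rule is written. What can be said is that no stated result could support the hypothesis.
- A reader might infer that sharing the t1 score biases follow-up towards a gain followed by a loss. Nothing in the plan makes t1 error differ by arm, and the t1–t2 test is not made conditional on a favourable t0–t1 result. The shared score gives a negative sampling correlation between the two estimates, not bias.
- A reader might infer that low power is peculiar to the planned test. A t0–t2 test also usually misses a remaining 3 points.

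**Conclusion.** The point holds for the ARAT and the secondary clinical outcomes. The only stated follow-up test has the trial's hypothesis as its null and no margin, and no stated test asks whether an arm difference remains at t2. That conclusion follows from the text alone.

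The size is less certain. With variance 26, a 6-point benefit at t1 and half of it lost, the t1–t2 test is non-significant in roughly 14 to 68% of trials at 15 to 17 per arm. The width of that range comes entirely from the assumed t1–t2 SD and measurement-error share. If DMCT catches up fully, the test is significant in over 90% under the measurement-error model (89% in the least favourable independent-change case), although trained patients lost nothing.

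The t0–t1 comparison is unaffected. This should be changed, but it does not undermine the primary result.

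**What to change.** Add to Outcome variables a between-arm comparison of t0–t2 change by the same rank-based procedure as t0–t1, with an estimated difference and confidence interval for each pair of arms. Base any statement that the benefit over DMCT is sustained on that estimate.

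Report t1–t2 change within each arm with a confidence interval. This shows whether patients kept their own gains, and whether a narrowing gap is loss or catch-up. State that a non-significant t1–t2 test will not be read as retention. Apply the same to the secondary clinical outcomes.

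The cost is a few sentences and one additional comparison per outcome, with no new visits or data. Power for a partial remaining benefit is modest, so the interval should carry the interpretation.
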